#### 3.2. FLOW CHART

[figure not shown]

## **4. POPULATION STUDIED**

### ***4.1. DESCRIPTION OF THE POPULATION***

Four hundred patients will be enrolled in this study, equally distributed in two groups (early versus progressive sitting). The targeted population will be of legal age, hospitalized for ischemic stroke in a Neurology unit the same day or the day after stroke onset (directly or through the emergency room or another unit). The study will be proposed and explained in the unit.

The protocol can be started in emergency, so that if the patient shows aphasia, the family can agree on the study after information and explanation (specific letters in annexes 7 and 9) As soon as the clinical state of the patient will be compatible with it, an informed consent will be obtained.

Patients included in the study won't be allowed to participate in another clinical study during the follow up time.

### ***4.2. PRE-INCLUSION CRITERIA***

NA

### ***4.3. INCLUSION CRITERIA***

- Aged 18 or above
- Persistent neurological deficit at the time of inclusion, caused by a diagnosed ischemic stroke (defined by a sudden neurological deficit without hemorrhage on the CT.
- Patients hospitalized in a Neurology unit the same day or the day after the neurological deficit (provided that the patient was left with the upper body inclined at 30° maximum up to that time)
- Health coverage

### ***4.4. EXCLUSION CRITERIA***

- Upfront severe stroke (malignant infarction, not alert with a GCS<13, cerebral herniation on imaging, vital prognosis at stake, NIHSS≥22)
- Fluctuating neurological deficit (increase/ decrease of the NIHSS of 4 points)
- Minor neurological deficit defined by isolated facial palsy (+/- dysarthria), isolated hemianopia, isolated sensitive deficit
- Known intra-cranial arterial stenosis >50%, symptomatic of the new symptomatology

- - History of neurological worsening in association with upright positioning
- - Situation that may alter the tolerance of early sitting: unstoppable vomiting or difficulty in breathing - Patient non autonomous before hospitalization (defined by a Rankin score>3, can't walk without assistance)
- - Deep vein thrombosis or suspicion.
- - Contra indication for early sitting, particularly in case of fracture
- - Patient of legal aged, with a legal guardian
- - Anticipated difficulty with the follow up
- - Participation to another clinical trial
- - Pregnant or breast feeding women
- - Patients who can't speak French
- - Not willing to sign the inform consent form

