#### **2.1.2. Primary outcome**

Functional prognosis at 3 months evaluated using the modified Rankin score. Proportions of Rankin score [0-2], which correspond to an autonomous life, will be compared between the two groups.

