### **5.3. IDENTIFICATION OF THE DATA COLLECTED OUTSIDE OF THE MEDICAL FILE**

- Blood pressure and heart rate during the sitting procedure
- Tolerance of the first sitting, with collection of any related side effect
- Barthel score at inclusion time, D7 (or last day of hospital) and 3 months
- Rankin score at inclusion time, D7 (or last day of hospital) and 3 months

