### **6.2.2. Statistical justification for the number of patients required**

In a meta-analysis of two pilot studies comparing an « early » to a « usual » mobilization procedure, Craig and coll. (9) showed that the percentage of patients with a Rankin score [0-2] was 34.7 % at 3 months in the « usual » group (n=49) versus 57.4 % in the « early » group (n=54).

In our study, we hypothesized that the functional outcome at 3 months assessed by the Rankin score will be better in the « early » group than in the « progressive » group, with a percentage of Rankin [0-2] of 35% in the « progressive » group and 50% in the « early » group. With an alpha risk of 5% and a power of 80% (bilateral), 183 patients per group are required to show a difference. Total number will then be 366 patients.

Percentage of poor tolerance during the first sitting is estimated between 5 and 10% in the 2 groups. As this may affect the Rankin score at 3 months, the number of patient to include has been increase to 400.

If the superiority of the « early » group is not statistically demonstrated, a switch to non inferiority could be undertaken. For this analysis, the non inferiority threshold is set at -5 % (maximum acceptable clinical difference). With 400 patients, non inferiority will be demonstrated if the real difference between the two groups is between 9 and 15%.

Reference: Committee for Proprietary Medical Products (CPMP). Points to consider on switching between superiority and non inferiority. 2000. European Medical Agencies (AMEA). CPMP/EWP/492/99.

The study will be undertaken in 11 centers. Each one, has the potential to recruit patients, with at least 300 cerebral infarction cases a year.

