## ***APPENDIX LIST***

Appendix 1 : Rankin score

Appendix 2 : NIHSS

Appendix 3: Barthel index

Appendix 6 : Information sheet for the patient

Appendix 7 : Information sheet in case of emergency

Appendix 8 : Patient's consent form

Appendix 9 : Consent form in case of emergency

## ***APPENDIX #1: RANKIN SCALE***

| Score | Symptoms                                                                                                              |
|--------------|------------------------------------------------------------------------------------------------------------------------------|
| 0            | None                                                                                                                         |
| 1            | No significant disability despite symptoms ; able to carry out all usual duties and activities                               |
| 2            | Slight disability ; unable to carry out all previous activities, but able to look after own affairs without assistance       |
| 3            | Moderate disability ; requiring some help, but able to walk without assistance                                               |
| 4            | Moderately severe disability ; unable to walk without assistance and unable to attend to own bodily needs without assistance |
| 5            | Severe disability ; bedridden, incontinent and requiring constant nursing care and attention                                 |
| 6            | Dead                                                                                                                         |

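### Patients already at Rankin 1–2 can be randomised, and the inclusion Rankin that identifies them is collected but left out of the primary analysis; stratifying on it would gain power without new data

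*Protocol*

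**What the plan says.** - **Entry (section 4.3).** The requirement is "Persistent neurological deficit at the time of inclusion, caused by a diagnosed ischemic stroke". No minimum score is attached.
- **Mild strokes (section 4.4).** Those excluded are "Minor neurological deficit defined by isolated facial palsy (+/- dysarthria), isolated hemianopia, isolated sensitive deficit". Severe strokes are excluded by a score (NIHSS 22 or more, GCS below 13); mild ones are not.
- **Rankin in eligibility (section 4.4).** The only rule concerns the state before the stroke: "Patient non autonomous before hospitalization (defined by a Rankin score>3, can't walk without assistance".
- **Endpoint (section 2.1.2).** "Proportions of Rankin score [0-2], which correspond to an autonomous life, will be compared between the two groups", assessed at 3 months. Appendix 1 defines grade 1 as "No significant disability despite symptoms".
- **Baseline data.** Sections 5.2 and 5.3 collect Rankin at entry: "Rankin score at inclusion time, D7 (or last day of hospital) and 3 months". NIHSS is also recorded at inclusion.
- **Analysis (section 6.2.1 and the abstract).** The primary test is a chi-square on the two proportions. A second-step logistic model adjusts for age and pre-stroke Rankin. Randomisation is not stratified (section 3.1). If superiority fails, the lower limit of the 95% confidence interval is compared with −5 points.
- **Sample size (section 6.2.2).** Planning is "with a percentage of Rankin [0-2] of 35% in the « progressive » group and 50% in the « early » group". The result is "With an alpha risk of 5% and a power of 80% (bilateral), 183 patients per group are required to show a difference", raised to 400 in total.

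**The concern.** A patient with slight arm drift, limb ataxia or mild aphasia who is rated Rankin 1 or 2 at inclusion passes every criterion and already meets the success definition. The binary endpoint can then record only retention or loss. If most such patients keep their success in both arms, their absolute treatment effect is probably smaller than that of the others. When more than 85% would succeed anyway, a 15-point gain is arithmetically impossible in that group.

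Two things follow. Inclusion Rankin is likely to be a strong predictor of the outcome, so leaving it out of the primary test gives away precision. And an overall difference averages a group with little room to gain with a group that has more, so harm confined to the more disabled patients could be partly hidden in the non-inferiority comparison.

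**Working it through.** **Inputs from the protocol.** 35% versus 50%; two-sided 5%; 80% power; 183 per group raised to 200; margin −5 points.

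**Assumptions, because the protocol gives no figure.** A share *s* enters at Rankin 1–2. Of these, 95% are at Rankin 0–2 at 3 months in both arms. *s* is taken as 10%, 20% and 30%.

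**1. The plan's own figure.** Uncorrected n = [1.960·√(2·0.425·0.575) + 0.842·√(0.35·0.65 + 0.50·0.50)]² / 0.15² = 169.3, so 170 per group. With continuity correction, n = (169.3/4)·[1 + √(1 + 4/(169.3·0.15))]² ≈ 182.4, so 183. The stated number reproduces. With 200 per group, the uncorrected chi-square has about 86% power.

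**2. Reading A: 35% versus 50% describes everyone enrolled.** The crude comparison is unchanged and power stays at 86% for any *s*. The effect required in the Rankin 3–5 patients becomes 15/(1 − *s*): 16.7, 18.8 and 21.4 points. For example, at *s* = 20% their rates are (0.35 − 0.19)/0.80 = 20.0% and (0.50 − 0.19)/0.80 = 38.75%. With 95% retention, a 35% overall control rate caps *s* at 0.35/0.95 ≈ 37%.

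**3. Reading B: 35% versus 50% describes only Rankin 3–5.** Control rate = 0.95*s* + 0.35(1 − *s*); difference = 15(1 − *s*) points. Crude power is by exact binomial enumeration.

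**4. Stratified test.** A Cochran-Mantel-Haenszel test with strata 0–2 and 3–5 at inclusion was simulated under both readings, with 200 per arm.

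| Share *s* | A: crude | A: stratified | B: control rate | B: difference (points) | B: crude | B: stratified |
|---|---|---|---|---|---|---|
| 10% | 86% | 90% | 41% | 13.5 | 78% | 82% |
| 20% | 86% | 95% | 47% | 12.0 | 68% | 76% |
| 30% | 86% | 99% | 53% | 10.5 | 56% | 69% |

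The gain is about 4, 9 and 13 points under A, and 4, 8 and 13 under B. One-sided error of the stratified test stays near 2.5%. Setting retention at 90% or 100% moves crude power under B by less than one point. If the mild patients instead share the planned odds ratio (0.50/0.50)/(0.35/0.65) = 1.86, crude power under B at *s* = 20% is 71–76% for retention of 95% down to 85%.

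**5. Non-inferiority, under B.**
- *Planned benefit.* The chance of meeting the −5 rule falls from 98% at *s* = 0 to 88% at *s* = 30%. Dilution makes non-inferiority harder here.
- *Harm confined to Rankin 3–5.* Suppose those patients lose exactly 5 points and the others nothing. The overall difference is −5(1 − *s*) = −4.5, −4.0 and −3.5 points. The rule is met in 3.2%, 3.9% and 4.9% of trials, against 2.5% at *s* = 0.
- *Opposite direction.* Section 6.2.5 counts an immediate lie-down as failure. If such events were 5 points more frequent in the early arm, they would cost about 0.05 × 90% = 4.5 points where success is 90%, but 0.05 × 35% = 1.75 points where it is 35%. Mild patients would then move the difference away from zero.

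**The case against.** **A reader might infer that the trial is underpowered.** The document does not support this. Section 6.2.2 gives 35% and 50% as the rates expected in this study, which most naturally means the population enrolled. Reading B implies control rates of 41%, 47% and 53%, which do not match the stated 35%. The fall below 80% is one assumed scenario. What stands is that section 6.2.2 does not say what share at Rankin 1–2 its rates allow for.

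**A reader might infer that false non-inferiority is inflated.** It is not. The margin applies to the overall difference, and −4.5, −4.0 and −3.5 points all lie inside −5. Meeting the rule there is no type I error for the stated comparison. Only the narrower point survives: the overall figure can mask harm in one subgroup.

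**A reader might infer that these patients are uninformative or should be kept out.** Preventing decline is a benefit, and neurological worsening is the main risk named in section 1.2.3; mild patients can show either. Rankin grades depend on everyday activity and walking, which are hard to judge in a patient kept in bed at 30° or less. As an entry limit, that early score would trade a narrower population for a doubtful gate. As a stratifier it only has to predict the outcome.

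**It can also be said that broad eligibility is a legitimate choice**, that section 4.4 did consider minor stroke, and that section 6.2.6 lets a later analysis plan modify the statistics. All true. But the protocol does fix the primary test and the adjustment covariates, and it passes over a baseline value that it already collects.

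**Conclusion.** The point holds as a missed improvement in the primary analysis, not as an error in the sample size or in the non-inferiority test. That patients at Rankin 1–2 can enter, and that inclusion Rankin is unused in the primary comparison, follows directly from the text. (Rankin 0 should not arise, since a persistent deficit is required.) The size is conditional. Planned power stands if the rates cover everyone enrolled; it would be about 78%, 68% or 56% if they cover only Rankin 3–5 and the share is 10%, 20% or 30%. The gain of about 4 to 13 points from stratifying holds on both readings. It rests on those assumed shares, on 95% retention in both arms, and on inclusion Rankin predicting the outcome as modelled. Masking of harm in the more disabled patients is possible, but its direction depends on where any effect lies.

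**What to change.** In section 6.2.1 and the matching part of the abstract, replace the crude chi-square by a Mantel-Haenszel test and risk difference stratified by inclusion Rankin (0–2 versus 3–5). Alternatively, add inclusion Rankin or NIHSS to the adjusted model and make that model the primary one. Fix the choice before outcome data are examined, and use the score recorded before allocation is known, since the trial is open.

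If the analysis moves to non-inferiority, report the Rankin 3–5 stratum beside the overall result, as description. The stratified risk difference still averages over strata, so it does not remove the masking. With harm of 5 points confined to Rankin 3–5, simulation puts the chance of meeting the −5 rule at 3.2%, 4.3% and 5.6%, slightly above the crude analysis, because the interval is narrower.

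In section 6.2.2, add a sentence giving the expected share at Rankin 1–2 on entry and saying whether 35% versus 50% includes them.

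The cost is analysis wording only: no new data, no new patients and no change to eligibility.

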## **5. STUDY PROCESS**

### **5.1. ANALYSES TOOLS AND PROCEDURES**

#### **5.1.1. Detailed description of the read outs**

##### Functional scale: modified Rankin score (annex #1)

The modified Rankin score is fast to perform, and gives a general assessment of the functional handicap of the patient, for everyday life. This scale is of common use for clinical trials.

This is a functional scale divided in 7 categories (0 to 6). A 0 score corresponds to an asymptomatic patient, and a score at 6 to a death. Between these extremes, the score varies according to the patient's ability in everyday activity.

##### Clinical scale : Score NIHSS (annex #2)

This is known and broadly used scale for neurological deficit evaluation, efficient and reproducible.

The NIHSS varies from 0 (no neurological sign) to 43 (the patient is not able to perform any of the tasks - quadriplegic)

##### Autonomy scale: The Barthel index (annex #3)

The good reproducibility of this index makes it a good tool for clinical trials.

This index assessed the autonomy of the patient, from 10 everyday-life tasks, dealing with self-care and mobility. The score varies from 100 (completely independent) to 0 (completely dependent), a score below 60 is associated with dependence in general.

##### Length of stay

Duration between hospital admission and exit.

#### **5.1.2. Description of the techniques used**

Early sitting: After an initial stage (the day of stroke onset) of lying with the upper body inclined at 30° maximum, the patient is seated out of bed at the earliest time, for a minimum duration of 15 minutes, under the supervision of the physiotherapist or the nurse. Sitting can be extended up to 60 minutes, if the tolerance is good. Blood pressure and heart rate will be recorded, before, immediately and 5 minutes after upright positioning. Sitting will be repeated everyday according to the same criteria, but the duration will be decided by the staff in charge.

Progressive sitting: After an initial stage (the day of stroke onset, D0) of lying with the upper body inclined at 30° maximum, the patient is seated in bed at 45 degrees (D1), then at 60 degrees (D2). The patient is not seated out of bed before the third day after stroke (D3), for a minimum duration of 15 minutes, under the supervision of the physiotherapist or the nurse (depending of the unit organization). Blood pressure and heart rate will be recorded, before, immediately and 5 minutes after upright positioning. Sitting will be repeated everyday according to the same criteria, but the duration will be decided by the staff in charge.

Supervision during the procedure : Any side effect that led to ceasing the procedure will be noted, for example neurological worsening (degradation of the current state or occurrence of new signs), persistent blood pressure surge (increase of 40mmHg so that the BP rises above 180/100), vagal reaction (bradycardia, nausea, sweat) or hypotension . Close neurological monitoring by the staff is required during the first 5 minutes of the sitting procedure.

Slighter side effects won't lead to the ceasing of the procedure: bearable headache, isolated nausea or vomiting.

## **5.2. STUDY SCHEDULE**

Screening: If the patient is eligible, written consent is obtained (from the patient directly or a relative otherwise)

### Inclusion visit:

Will be documented:

- Demographic data
  - Date of birth
  - Gender
  - Former autonomy level (Rankin score before stroke onset)
  - Living: location (at home/specialized institution), alone/significant other
- Clinical data
  - Cardio-vascular risk factors
  - History of coronaropathy, arteritis
  - Date and time of the qualifying event
  - Symptoms
  - NIHSS
  - Rankin score
  - Barthel score
- Arm in which the patient is enrolled
- Current treatments (anti-hypertensive drugs, psychoactive drugs, blood thinner)

### Early sitting (D1 or D3 according to the group)

- Tolerance, potential side effects
- Blood pressure, heart beat, before, immediately and 5 minutes after upright positioning
- Duration of the upright positioning

### According to the group affiliation:

- Early sitting:
  - Duration of the lying down at 30° (D0)
  - Time and duration of the first sitting
  -
- Progressive sitting:
  - Duration of the lying down at 30° (D0)
  - Time with 45 degrees positioning (D1)
  - Time with 60 degrees positioning (D2)
  - Time and duration of the first sitting (D3)

### 7 day visit (or before exiting the hospital if before D7)

Will be documented:

- Clinical data

- NIHSS
- Rankin score
- Barthel score

Exit of the hospital:

- Cause of the cerebral infarction, if available
- Internal carotid artery status (ultra sounds)
- Date
- Orientation of the patient (back home, rehabilitation, ...)
- Immobility related complications during hospitalization

3 month visit

Will be documented:

- Clinical data
  - NIHSS
  - Rankin score
  - Barthel score
- Cause of the cerebral infarction
- Presence/Absence of post stroke fatigue
- Synthesis about complications that occurred during the hospital stay

**STUDY SCHEDULE**

| Actions                                                                                       | D0
(Inclusion) | First
sitting | D7 or the last day of
hospitalization | M3 |
|------------------------------------------------------------------------------------------------------|---------------------------|--------------------------|---------------------------------------------------------|-----------|
| Information of the patient (or relative) / written
informed consent patient (or relative) | X                         |                          |                                                         |           |
| Medical history                                                                               | X                         |                          |                                                         |           |
| Clinical exam (Rankin score, NIHSS, Barthel
index)                                         | X                         |                          | X                                                       | X         |
| Documentation:
- Cause of the cerebral infarction
- Ultra sound results                 |                           |                          | X                                                       |           |
| Monitoring: blood pressure, heart rate, clinical
exam                                     |                           | X                        |                                                         |           |

### **5.3. IDENTIFICATION OF THE DATA COLLECTED OUTSIDE OF THE MEDICAL FILE**

- Blood pressure and heart rate during the sitting procedure
- Tolerance of the first sitting, with collection of any related side effect
- Barthel score at inclusion time, D7 (or last day of hospital) and 3 months
- Rankin score at inclusion time, D7 (or last day of hospital) and 3 months

### **5.4. CRITERIA FOR WITHOLDING THE PARTICIPATION OF A PATIENT**

#### **5.4.1. Precocious stop of a patient participation**

Precious stop of a patient participation is defined by:

- ❖ Investigator's decision
- ❖ Patient's withdrawal of his consent, at any stage of the study. No justification is required. In the particular case of a consent given by a relative (emergency situation), this person has authority to decide to stop the patient's participation to the study, without penalty or prejudice.
- ❖ Serious complication not compatible with the continuation of the study
- ❖ Patient for whom an unexpected event occurs and is not compatible with the study continuation, as defined in the protocol (death of another cause, occurrence of a clinical situation whose management is not compatible with the continuation of the study).

#### **5.4.2. Procedure**

For the modality and follow up duration of the patients in case of a precocious stop of the participation in the study, refer to the statistical section.

In case of a precocious stop of a patient's participation to the SEVEL study, the investigator is in charge of collecting as much information as possible regarding the causes and the situation.

